#### MRI T1ρ cartilage mapping

The association between hip arthroscopy outcomes and cartilage quality is not well elucidated in the literature. The quality of the hip articular cartilage will be assessed by a non-invasive and validated MRI technique called T1ρ mapping that enables the evaluation of proteoglycan content [55, 56]. The cartilage will be segmented on co-registered anatomical MR images and quantitative cartilage T1ρ values will be measured in six regions over the cartilage [57]. The T1ρ relaxation time is sensitive to the cartilage proteoglycan content and increasing when the proteoglycan content is decreasing. We will compare the cartilage T1ρ relaxation times at the initial scan and at the follow-up scan (24 months after surgery) in the different regions to investigate changes in the cartilage macromolecule content after surgery. The significance of the differences in T1ρ will be tested using a paired t-test with a significance level of *p* < 0.05.

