### Sample size and power calculation

A total sample size of 126 subjects is planned. Calculation of the required sample size is based on ensuring sufficient statistical power to detect a difference in the primary outcome measure (i.e., iHOT-33) at 12 months. The standard deviation of the iHOT-33 is approximately 16 in pre-arthritic patients [66–68]. The original iHOT-33 manuscript reported a minimal clinically important difference (MCID) of 6.1 in a general symptomatic hip population [66]. Since then, three other studies focusing on hip arthroscopy reported MCIDs varying from 10 to 12 [67–69] in time ranges varying from 6 to 12 months. Using a non-central *t* function with a conservative MCID of 10, an alpha level of 0.05, a power of 0.90, and a loss to follow-up of 15% provides a total sample size of 63 per group (total of 126).

For the T1ρ analysis, part of the subjects from each of the two subgroups will undergo quantitative hip cartilage MRI T1ρ-mapping. Our group has shown T1ρ to be a valid alternative to the gold standard (dGemric) for patients with symptomatic hip dysplasia (Additional file 1). Based on our hypothesis that patients undergoing in arthroscopy+PAO will conserve cartilage characteristics, whereas those with PAO only will demonstrate affected cartilage, the sample size for this study is calculated using a power analysis on T1ρ data from our longitudinal cartilage T1ρ study (two time points, mean follow-up time of 24.5 months) on corrective surgery for cam deformity in association with FAI [70]. Two years after surgery, T1ρ decreased significantly (*p* < 0.05) in the anterosuperior area of cartilage from 34.6 to 29.4 ms reaching control T1ρ values. By assuming a standard deviation of the mean T1ρ value of 5%, a power of 0.9, and alpha error of 0.05, we calculated that 21 subjects are needed for each of the two subgroups. Based on the follow-up loss rates from the former study (5 of 24; 20%) with this patient population, we will recruit a total of 26 patients per subgroup which will undergo the additional cartilage T1ρ-mapping protocol [57].

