### Analyses and frequency of analyses

The analysis will be conducted on an intention-to-treat basis. Statistical analyses will be performed blinded to treatment allocation. A level of significance of 0.05 will be used for all analyses. The underlying assumptions of all statistical procedures will be evaluated, and data transformation will be considered. Using descriptive statistics, baseline patient characteristic differences between the study groups will be assessed (age, sex, outcomes) and differences will be controlled for in the statistical analyses. Repeated measures mixed models and general linear mixed models will be used for handling continuous and dichotomous outcomes respectively. Sex will be specifically assessed as an effect modifier in the analyses. Multiple imputation will be considered as a sensitivity analysis.

For cartilage health, the biochemical content of the cartilage will be evaluated using MRI T1ρ mapping. The scan will be performed pre- and 2 years after surgery using a 3D turbo spin echo acquisition method with T1ρ preparation (CUBE QUANT) and the following parameters: TR = 1350 ms, TEeff = 40 ms, FOV = 25.6 × 25.6 cm^2^, in-plane resolution = 0.5 × 0.5 mm^2^, slice thickness = 3 mm, number of slices = 32 slices, no slice gap (3D sequence), B1 = 500 Hz, spin-lock times = 1, 15, 30, 45 ms, and scan time = 18 min [56, 71] (Additional file 1, Figure 3). For post-pressing, T1ρ-weighted datasets will be co-registered to the proton density-weighted turbo spin echo images and analyses described in our previous publications [57, 70]. The hip cartilage will be divided in six regions of interest (ROIs): anterior lateral, anterior middle, anterior medial, posterior lateral, posterior middle, and posterior lateral for regional proteoglycan assessment [57]. T1ρ values from the different cartilage regions will be compared and evaluated for significant differences between the pre-operative and the follow-up scan using repeated measures analysis of variance (ANOVA).

In addition to the final analysis, an interim analysis will be performed after 2.5 years to determine if the study must be terminated. This will be based on the following results: serious adverse events significantly higher in the experimental group, greater than expected beneficial effects, improbable statistically significant difference by the end of the study, and participant recruitment is severely lagging and unlikely to achieve the target.

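### The T1ρ sub-study is sized as one comparison in one cartilage area but analysed over six regions at an unadjusted 0.05, with no decisive region, a faulty region list and two different tests named

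*Protocol article*

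**What the plan says.** Four sections of the protocol article bear on this point.

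- **Principal research questions.** Cartilage health stands beside quality of life in the primary objective. The hypothesis is that adding arthroscopy prevents further cartilage damage compared with PAO alone.
- **MRI T1ρ cartilage mapping** (under Secondary outcome measures). "quantitative cartilage T1ρ values will be measured in six regions over the cartilage". Baseline and 24-month values are compared in the different regions, and the differences "will be tested using a paired t-test with a significance level of" 0.05.
- **Sample size and power calculation.** The sub-study is sized on an earlier series in which T1ρ fell "in the anterosuperior area of cartilage from 34.6 to 29.4 ms reaching control T1ρ values". The remaining inputs are given as "By assuming a standard deviation of the mean T1ρ value of 5%, a power of 0.9, and alpha error of 0.05". The result is 21 per subgroup, raised to 26 for loss to follow-up.
- **Analyses and frequency of analyses.** "A level of significance of 0.05 will be used for all analyses". The regions are "anterior lateral, anterior middle, anterior medial, posterior lateral, posterior middle, and posterior lateral for regional proteoglycan assessment". Regional values before surgery and at follow-up are then compared by repeated measures ANOVA, not by the paired t-test named in the outcome section.

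No section names a decisive region, states a multiplicity rule for the regions, or says which listed region or regions make up the anterosuperior area.

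**The concern.** The sizing presumes one test in one place, while the analysis allows up to six at the same 0.05. The protocol therefore does not fix in advance which result would support or refute the cartilage hypothesis, and any region that reaches significance could be put forward as the answer. Because cartilage health is in the primary objective and the sub-study has its own power calculation, readers will treat the T1ρ result as more than descriptive.

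Two faults in the text add to this. The printed list has six entries but five distinct names, so it does not deliver the six regions promised. And the area that supplied the effect size has no stated counterpart among the regions to be analysed, so the stated power is not tied to a defined endpoint.

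**Working it through.** **1. The plan's own figure: 21 per subgroup.**

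Inputs, all from the sample size section: difference 34.6 − 29.4 = 5.2 ms; standard deviation 5% of the mean T1ρ value; power 0.9; alpha 0.05 (sidedness not stated).

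- Read literally, the standard deviation is 0.05 × 29.4 = 1.47 ms to 0.05 × 34.6 = 1.73 ms. Every variant tried (one- or two-sided, two-sample or paired, normal or t) then gives only 2 to 4 subjects per group, so 21 does not reproduce.
- Read as 5 ms, the normal formula for two means gives n = 2 × (1.960 + 1.282)² × 5² / 5.2² = 19.4, so 20. The two-sided two-sample t-test gives 21, with power 0.908.
- Loss: 21 × 1.20 = 25.2, so 26 as stated; 21 / 0.80 = 26.25, so 27. One patient is immaterial here.

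Of the readings tried, the only one that returns 21 is 5 ms with one two-sided, two-sample test at 0.05. That is an inference about what was done, not something the protocol states. On that reading the sizing allows for a single comparison.

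**2. The region list.**

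| Position | Printed name |
|---|---|
| 1 | anterior lateral |
| 2 | anterior middle |
| 3 | anterior medial |
| 4 | posterior lateral |
| 5 | posterior middle |
| 6 | posterior lateral (repeat of 4) |

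The anterior entries run lateral, middle, medial. The same pattern would make entry 6 posterior medial. No entry is called anterosuperior.

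**3. Error rate if the regions are tested separately at 0.05.**

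Suppose T1ρ truly changes in none of the regions.

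- Six independent tests: 1 − 0.95⁶ = 0.265.
- Five distinct names, taking the list literally: 1 − 0.95⁵ = 0.226.
- Six correlated tests, simulated as equicorrelated normal statistics (two-sided 0.05, 400,000 draws). The protocol gives no between-region correlation, so a range is shown:

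| Assumed correlation | Chance of at least one false-positive region |
|---|---|
| 0.3 | 0.24 |
| 0.5 | 0.21 |
| 0.7 | 0.16 |
| 0.9 | 0.11 |

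Every value exceeds 0.05; the lowest is about twice it.

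**4. What full adjustment would cost, for scale.**

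Take the 5 ms reading and a Bonferroni level of 0.05 / 6 = 0.0083. The two-sample t-test then needs 31 evaluable per group, or 31 / 0.80 = 38.75, so 39 recruited. With 21 evaluable per group, power at that level is about 72%. One pre-specified comparison at 0.05 leaves the requirement at 21.

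**The case against.** **Secondary endpoint, detail for the SAP.** The only primary outcome is iHOT-33 at 12 months, and T1ρ is a sub-study of 26 per arm. A multiplicity rule within such an endpoint is often left to the SAP. This stands as a reason for modest severity. It does not remove the point, because the protocol is not silent: it sets 0.05 for everything, sizes on one area and prints a faulty list.

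**The ANOVA may be one omnibus test.** This is a fair reading of the analysis section, and under it the regional error rates above would not apply to that test. But the outcome section prescribes paired t-tests in the different regions, so the two sections disagree. An omnibus test would also not tie the conclusion to the area used for sizing.

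**A reader might infer a 26% chance of falsely concluding that arthroscopy protects cartilage.** The documents do not support that. Both tests written specifically for T1ρ compare the pre-operative with the follow-up scan, and a pre-post change in a region is not a difference between arms. The 26% also needs independent regions within one joint, which is unlikely.

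**A reader might infer that the anterosuperior area is not measured, or that only five regions are.** Neither follows. Three listed regions are anterior and may contain the area, and the article refers the image analysis to earlier publications that include the sizing study. The fault is a mapping not stated. The repeated name is most likely a slip, since both sections speak of six regions; alone it has little statistical consequence.

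**Conclusion.** The point holds in a limited form. As written, the protocol allows up to six regional T1ρ tests at an unadjusted 0.05 for a sub-study sized on one comparison. It names no decisive region, does not map the sizing area to the regions, repeats one region name, and names two different tests.

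If regions are tested separately, the chance of at least one false-positive region is 26% under independence and roughly 11% to 24% over assumed correlations of 0.9 down to 0.3. These figures assume no true change in any region and equal correlation between regions. They describe the regional tests as stated; they would describe the arthroscopy-versus-control claim only if it too were tested region by region.

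Severity is minor to moderate: T1ρ is listed as a secondary outcome, and the iHOT-33 analysis is untouched.

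**What to change.** 1. Correct the region list; the sponsor should confirm that the sixth entry is meant to be posterior medial.
2. Reconcile the paired t-test in the outcome section with the repeated measures ANOVA in the analysis section, and say whether inference is omnibus or per region.
3. Pre-specify one primary T1ρ measure: the region, or combination of regions, that the sponsor maps to the anterosuperior area of the sizing study. The documents do not supply this mapping, so it has to come from the sponsor, and before the follow-up scans are analysed.
4. Base the cartilage conclusion on the between-arm comparison of that measure at 0.05.
5. Report the other regions as exploratory, or with a Holm correction.

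The cost is wording only. On the 5 ms reading the requirement stays at 21 per group, with no added patients or scans. The downside is that an effect confined to another region becomes exploratory.

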### Confidentiality and retention of records

To maintain confidentiality of participant data, a data management plan will be developed and approved by the coordinating center. Study participant medical information obtained by this study is confidential, and disclosure to third parties other than those noted in the Informed Consent Document is prohibited. All local and federal guidelines and regulations regarding maintaining study participant confidentiality of data will be adhered to. Data generated by this study must be available for inspection by representatives of the Coordinating Center or their representative, Study Monitoring personnel, and the IRBs.

Each participating center is responsible for tracking all of their enrolled patients and storing paper records according to local IRB guidelines. The master study database containing participant information will be stored in a password-protected excel file stored in the secure, in-house hospital server at the coordinating center. The password will only be known to members of the approved study team.

Participants will not be identifiable in any publications or presentations resulting from this RCT study. No identifying information will leave the participating center. All information which leaves the participating centers will be coded with an independent study number.

Research records will be retained in accordance with site IRB policies. The starting date used to calculate the retention period is the date when a record is first created. All paper records will be stored in a securely locked office by the participating center study coordinators. Upon receiving data from the participating centers, all electronic records will be stored on the OHRI secure server which is physically and virtually protected.

### Secondary use of data

Any secondary use of data for a purpose other than what is listed in the study protocol will require additional ethics approval. If the new purpose is to obtain data not yet collected from participants, it will require re-consenting of all existing study participants.

#### Protocol amendments

Should any amendments or modifications to the study protocol be necessary during the course of the study, a protocol amendment submission will be made to the REB of the lead site. Once approved, the details of the protocol amendment will be communicated directly to the designated study coordinators at each participating site via email. If the amendments will have any effect on the patients already enrolled in the study, they will be notified by telephone by the study coordinator at each site. Any trial registries or journals that have published the protocol will also be notified of the amendments via the agency’s approved notification mechanism.

#### Post-trial care

All participants will continue to receive medical care from their treating surgeon after trial completion, as necessary. The are no provisions for providing compensation for patients who suffer harm from participation in the trial.

#### Authorship

Authorship for any trial publications will be based the authorship guidelines of the publication. In general, authors must have materially contributed to any or all of the following study aspects: protocol design, treatment provision, data analysis, manuscript preparation, and critical review. There is no intention to use professional writers.

## Discussion

### Planned recruitment rate, organization, and time period

As aforementioned, we have already obtained Research Ethics Board approval for our feasibility trial. An amendment will be submitted at the lead site and Centre Hospitalier Universitaire de Québec, to add the T1ρ component. We estimate that approval of this amendment will take 2 to 3 months at both sites. Since January 2019, we have recruited 36 patients overall across four sites as part of the feasibility cohort (on average 6 patients per month). Based on similar studies completed by this multidisciplinary study team, an average recruitment rate of 8–10 patients per month is more than feasible as the recruitment strategy is optimized with proper human resources [72, 73].

Enrolling patients from four centers will allow sufficient numbers in an adequate timeframe to achieve power in our statistical analyses. Multiple participating centers/surgeons will also improve the applicability of the results and translation of the findings to various surgeon practices and patient populations. An average of 60 PAOs are performed at each US site and approximately 40 PAOs are performed at each Canadian site per year, thus providing approximately 200 potentially eligible patients for recruitment per year. Including Washington University in St. Louis Missouri and the William Beaumont Hospital in Detroit Michigan will allow us to achieve timely recruitment rates, due to their higher volume. Including Centre Hospitalier Universitaire de Québec will allow a broader Canadian perspective. Involving sites across North America will allow for stronger generalizability of study findings. We expect a comparable consent rate for the proposed randomized control trial as for the feasibility pilot at 72 patients per year. Taking into account an eligibility rate of 75% and a consent rate of 60%, recruitment will take 1.5 years to complete (Additional file 10), with 126 patients needed to achieve sufficient statistical power.

Subjects will be recruited prospectively from the surgical practices of the participating surgeons at the participating sites. All patients that meet the inclusion criteria (above) will be considered for enrollment. The total number of patients considered for enrollment will be recorded, whether or not they are eventually included in the research study. For patients that meet the inclusion/exclusion criteria, the surgeon will provide a brief description of the study as well as a relevant discussion of the surgical risks and benefits of hip arthroscopy and periacetabular osteotomy. Patients that express interest in participation will then be contacted by the surgeon’s Clinical Research Coordinator who will re-confirm eligibility and provide a detailed description of the study and obtain written informed consent for participation (see Informed Consent Form used for pilot study in additional attachments). Once patient consent to participate in the study has been obtained, the patient will complete a surgical consent form with the procedure listed as “[Left/Right] periacetabular osteotomy, +/− hip arthroscopy.” Participation is voluntary and patients may withdraw consent for participation at any time.

Patients recruited in the T1ρ analysis will be recruited from the above cohort at The Ottawa Hospital and at the Centre Hospitalier Universitaire de Québec over the span of one and a half years. The patient will be invited to be additionally assessed with T1ρ. This will leave 4 years to complete the collection of all primary and secondary outcome measures, to reach the primary endpoint of 2 years. The cost-utility analysis will occur in years 4 and 5 (see Additional file 10).

### Anticipated compliance problems

We do not anticipate compliance problems, as the interventions are one-time surgeries. If patients cross over from one treatment group to another after randomization, their results will still be included in the final analysis on an intention-to-treat basis. All attempts should be made to avoid patient cross-over and if cross-overs do occur after randomization, the reason for this will be recorded. The aim of the pilot was to test the methods and optimize data collection procedures. If that data is shown to be applicable to the current proposal, it will be included.

### Anticipated loss to follow-up rate

Compliance with all follow-up assessments will be ensured by the Clinical Research Coordinator and each participating site and may include contacting patients by phone and/or email to ensure compliance with follow-up assessments. If patients withdraw from participation prior to surgery, they will not be included in the final analysis. If patients withdraw from participation after surgery, the outcome scores completed prior to their withdrawal will be included in the final analysis. It is anticipated the loss of follow-up will be around 15%, with around 20% for imaging at 2 years. This is based on loss to follow-up rates seen in similar trials with similar follow-up periods [41, 70]. Randomized controlled trials accomplished at our site have also typically seen 15% loss to follow-up rates.

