### Randomization

Randomization will be carried out in blocks randomly varying between 2 and 4 to ensure equal numbers in both treatment arms (i.e., “PAO” and “Scope-PAO”). Randomization will be stratified by recruiting site to allow for even distribution of intervention covariates and patient characteristics across each site and by sex to ensure adequate distribution of this variable for the analyses. Patients will be randomized just after enrolment, because MRI sensitivity is inadequate to identify intraarticular pathologies [28]. This will allow the surgeon’s office and treating institution to appropriately plan for the required surgical intervention, necessary equipment, operating room time, etc. Patients will be randomized through an on-line computer randomization program that will be accessible by designated research staff from all participating sites.

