### Proposed methods for protecting against sources of bias

The addition of hip arthroscopy represents a discrete intervention added on to the current standard of care for treatment of symptomatic hip dysplasia (i.e., PAO). Thus, a randomized trial represents the best study design for assessing its potential additive effect. Since the treating surgeon must administer the experimental intervention, a double-blind design is not possible.

Assessments that are not patient self-report and data analyses will be performed blinded to allocation. When submitting our feasibility protocol to our Research Ethics Board in the spring of 2018, we initially had indicated blinding of study participants through a diagnostic arthroscopy in the PAO-only patients (same incision as PAO+arthroscopy group). However, there were ethical implications with inserting a scope into the hip of the control group and therefore we converted the study design to a single-blinded methodology only, recognizing that this may introduce a potential source of bias in any patient-reported outcome measures. In addition to patient-reported outcomes, objective performance measurements, administered by blinded assessors, will be performed as one of the outcome measures. At each postoperative time point, patients will document through a standardized form conservative and surgical co-interventions targeting the treated hip and received after the previous time point.

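### Patients who withdraw between randomisation and surgery are dropped from the final analysis, which contradicts the declared intention-to-treat analysis

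*Protocol article*

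**What the plan says.** Under Analyses and frequency of analyses, the protocol article states without qualification: "The analysis will be conducted on an intention-to-treat basis". Under Anticipated compliance problems it applies this to patients who cross over: "their results will still be included in the final analysis on an intention-to-treat basis".

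Under Anticipated loss to follow-up rate it gives two rules for withdrawal. Before surgery: "If patients withdraw from participation prior to surgery, they will not be included in the final analysis". After surgery: "If patients withdraw from participation after surgery, the outcome scores completed prior to their withdrawal will be included in the final analysis".

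The Randomization section fixes the timing: "Patients will be randomized just after enrolment, because MRI sensitivity is inadequate to identify intraarticular pathologies". It gives a practical reason as well: "This will allow the surgeon’s office and treating institution to appropriately plan for the required surgical intervention".

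Under Proposed methods for protecting against sources of bias, the article explains that blinding of participants was given up: "we converted the study design to a single-blinded methodology only". What remains blinded are the assessments that are not self-reported and the data analyses. The primary outcome, the iHOT-33, is self-reported. It is collected before surgery and at 6, 12 (primary) and 24 months after it.

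**The concern.** Intention-to-treat keeps the arms as randomisation formed them. Here one class of randomised patients is removed for something that happens after allocation, in the interval between enrolment and surgery. The reason for leaving may be unrelated to the arm. It may also be the arm itself, such as disappointment at not receiving arthroscopy or reluctance to have the added procedure. If the reason differs between arms, the patients analysed are no longer comparable by design and the 12-month iHOT-33 contrast can be biased.

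The two statements also cannot both be followed. An analysis plan that obeys the withdrawal rule breaks the intention-to-treat statement, and the reverse. The conflict lies in a stated rule, so it is not a matter of detail left to a later document.

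**Working it through.** **1. The rules side by side**

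| Patient, after randomisation | Rule in the article | Consistent with intention-to-treat? |
|---|---|---|
| Crosses over | Kept, by intention-to-treat | Yes |
| Withdraws after surgery | Scores up to withdrawal kept | Yes |
| Withdraws before surgery | Not in the final analysis | No |

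Only the third row departs from the declared population. It is not limited by arm, by reason, or to withdrawal of consent to use data.

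**2. Can the exclusion depend on the arm?** Randomisation follows enrolment directly, the surgeon's office plans the operation from the allocation, and participants are not blinded. The patient and the surgeon, whose decisions lead to withdrawal, are therefore outside the blinding. No section says outright that patients are told their arm before surgery. Dependence on allocation is possible, not demonstrated.

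**3. The plan's own sample size.** Inputs from Sample size and power calculation: difference 10, SD 16, alpha 0.05 (two-sided assumed, since that reproduces the figure), power 0.90, loss 15%. The noncentral t calculation with d = 10/16 = 0.625 gives 54.78 per arm, and 54.78 × 1.15 = 62.99, so 63 per group and 126 in total. The stated figure reproduces and is not in dispute.

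**4. Illustrative bias.** The article gives no pre-surgery withdrawal rate, so both inputs here are assumptions. Let a share f of one arm be removed, and let those patients differ by g points on average from the patients retained in that arm. The mean of the whole arm equals the retained mean plus f × g, so the bias in the contrast is f × g in size:

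- f = 5%, g = 10: 0.5 points
- f = 5%, g = 20: 1.0 point
- f = 10%, g = 10: 1.0 point
- f = 10%, g = 20: 2.0 points

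Against the 10-point target this is 5–20%.

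**5. Effect on the false-positive rate in the same scenarios.** With 15% loss the intact arm has 63 × 0.85 = 53.55 analysable patients. The reduced arm has 50.9 (f = 5%) or 48.2 (f = 10%). For f = 10% and g = 20, the standard error is 16 × √(1/53.55 + 1/48.2) = 3.18, the noncentrality is 2.0/3.18 = 0.63, and the two-sided error is 9.6% instead of 5%. For a bias of 0.5 points it is 5.3%, and for 1.0 point about 6.1%.

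**6. Power.** If the removals come on top of the 15% loss (the article does not say whether the 15% includes them) and fall equally on both arms, power is 89.3% with none removed, 87.7% with 5% removed and 85.9% with 10% removed.

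**7. Would keeping these patients through their baseline score help?** In a model with a common baseline mean and common slope b, each arm's estimated 12-month mean is its observed mean plus b × (overall baseline mean − that arm's baseline mean among patients with follow-up). Patients with a baseline score only enter through the overall baseline mean, which cancels in the difference between arms. The estimate is then the same as the baseline-adjusted estimate that leaves them out. A simulation with baseline correlations of 0.3 and 0.5 confirmed this: when g was unrelated to baseline, the two estimates agreed and the whole f × g bias remained in both. Only observed 12-month scores removed it.

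**The case against.** The strongest reply is that the exception is narrow. It covers patients who leave the study. Those who stay but do not receive the allocated procedure fall under the cross-over rule and are kept. Someone who has withdrawn consent cannot be made to complete a questionnaire and has at most a pre-operative score. On this view the bias in steps 4 and 5 is the cost of missing outcomes and not of the sentence, and striking the sentence alone would change the 12-month contrast very little.

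Much of this stands. Step 7 confirms the last part, and withdrawal of consent to data use is a legitimate exception. But the sentence is not confined to that case. It takes withdrawal before surgery as sufficient reason to leave the analysis, so it gives sites no reason to seek follow-up from patients who would still provide it.

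Three stronger readings are tempting and are not supported:

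- A reader might infer that the exclusion will be driven by allocation, or that the trial is simply unblinded. The article describes a single-blinded trial with blinded analyses and blinded objective assessments, and the surgical consent form lists arthroscopy only as a possible addition.
- A reader might take the 0.5–2.0 points as an estimate for this trial. It rests on assumed inputs with all removal placed in one arm.
- A reader might tie in the pilot clause, "If that data is shown to be applicable to the current proposal, it will be included". That is a separate question. It follows a sentence about testing methods and data collection, and nothing says that the decision would be made on results by arm.

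**Conclusion.** The contradiction holds on the text alone. The article declares intention-to-treat, randomises before surgery, and then removes randomised patients who withdraw before surgery, without calling the result modified intention-to-treat. This needs correcting because it defines the primary analysis population, whatever the number of patients affected.

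The numerical consequence is unknown. Under the assumed 5–10% one-arm removal and a 10–20 point difference, the bias is 0.5–2.0 points and the false-positive rate about 5.3% to 9.6%. The loss of power is modest. The documents allow the exclusion to depend on allocation but do not show that it will.

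**What to change.** Replace the sentence under Anticipated loss to follow-up rate with:

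*All randomised patients are analysed in the arm to which they were randomised, including those who withdraw before surgery, except where consent to use of data is withdrawn.*

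With it:

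- Separate not having surgery from stopping data collection. Ask non-operated patients who agree to complete the 12-month iHOT-33. The follow-up times are counted from surgery, so state the date from which the 12 months run for a patient who has none.
- Do not rely on baseline-only inclusion as the remedy. It restores the population on paper but leaves the bias.
- If an operated-only set is wanted, label it modified intention-to-treat and use it as a sensitivity analysis.

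The cost is one protocol sentence and a few extra questionnaires. The planned 126 patients are unchanged.
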